## Methods and design

### Design

We will conduct our study in a naturalistic–pragmatic design, replicating everyday clinical practice conditions and thereby enhancing its external validity (50, 51). The evidence suggests that well-designed naturalistic studies, compared with RCTs (52–54), can provide evidence without overestimating effect sizes (internal validity), and they can address difficult-to-investigate trial questions, such as those related to public sector services (25). The study is a quasi-experimental pragmatic trial with two groups: an intervention group and a treatment as usual (TAU) group. The treatments for both groups (the intervention group and the TAU group) will be provided at public health hospitals. The intervention group will attend the STP-BPD of the 1^st^ Department of Psychiatry, Medical School, National and Kapodistrian University of Athens, Eginition Hospital. The TAU group will take place in two centers: the Outpatient Clinic for Borderline Personality Disorder Patients of the 2^nd^ Department of Psychiatry Medical School, the Attikon General University Hospital of the School of Medicine (TAU1), and the Outpatient Clinic for Borderline Personality Disorder Patients of the Psychiatric Clinic of the Sismanogleion General Hospital (TAU2). The study established both TAU centers, as detailed below.

We designed this study to evaluate the effectiveness and economic aspects (cost-effectiveness and cost-utility) of the STP-BPD in everyday clinical practice, adhering to the call for *‘real-world’* clinical trials (55, 56). Therefore, we will use minimal exclusion criteria without altering clinical decision-making, health care, or treatment. Patients will be followed for 2 years for primary and secondary outcomes, and for additional 3 years for primary outcomes only. Assessment of the clinical and psychosocial outcome variables will be performed at baseline (T_0_), prior to patient allocation, and every 6 months until the end of the 2^nd^ year of follow-up (T_1_, T_2_, T_3_, and τ_4_). At baseline (T0) and then every year thereafter (τ2 and τ4), the mediators that affect the link between the type of health care service and the major clinical and psychosocial outcomes will be examined. For long-term evaluation, primary outcome variables will also be assessed at T_5_ (2 years and 6 months), T_6_ (3 years), T_7_ (3 years and 6 months), T_8_ (4 years), T_9_ (4 years and 6 months) and T_10_ (5 years). Patient flow, screening and assessments are displayed schematically in **Figure 1**.

**Figure 1 f1:**
[figure not shown]
Flowchart of the study design.

Primary outcomes will be (i) the severity of BPD symptoms and (ii) the severity of self-harm and suicidality. Secondary outcomes will be: (i) psychopathological symptom severity, (ii) quality of life, (iii) quality and intensity of interpersonal relations, (iv) functioning and (v) disability.

Mediator variables will be: (i) reflective functioning, (ii) defense style and (iii) personality organization. In other words, better primary and secondary outcomes for the intervention group as opposed to TAU group are expected to be discerned due to differences in reflective functioning, defense style and personality organization. As the design does not include random allocation of participants in the two arms, baseline measurements of the outcome variables will be considered as confounders for the ensuing measurements. Moreover, the two groups will be compared in terms of the following variables: sex, family status, education status, number of children, profession, living arrangement, physical illness, medication for BPD and prior hospitalize physical illness, medication for BPD and prior hospitalization. Those variables with a statistically significant difference between the two groups, will be considered confounder variables in the design and will be taken into consideration as such in ensuing evaluation points. Moreover, information about the treatment delivered in the two groups will be recorded; namely, duration of treatment, type and number of sessions attended. These will be included as confounder variables in the design.

The Ethics Committees of Eginition Hospital, Medical School of the National and Kapodistrian University of Athens (No. 404/05-07-2021), Attikon Hospital (No. 443 25/08/2021), and Sismanogleion General Hospital (27703/10-12-2021) approved the research protocol. The Clinical Trials.gov website has registered the trial under the ID NCT06392139 (Protocol ID No. 404/06-07-202).

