### Recruitment

Patients will be recruited from the participating centers. The STP-BPD at the Eginition Hospital receives referrals from public sector psychiatric health services and mental health private practitioners from Athens and the surrounding area. Occasionally, the program receives referrals from other regions of Greece, but for acceptance, a patient must maintain residency in Athens for a minimum of 2 years. The two TAU centers receive referrals from the psychiatric emergency room, inpatient psychiatric unit, or other outpatient clinics of the two hospitals (the Attikon General University Hospital and the Sismanogleion General Hospital, respectively). They also receive referrals from private mental health practitioners. The two TAU centers are located in different areas of Athens, TAU1 in the northern suburbs of Athens and TAU2 in the western suburbs of Athens, thus covering a population from a wide area of Athens and its surroundings with different socioeconomic characteristics. Patients who are already receiving BPD treatment at participating centers will not be included in the study.

All potential participants will be given verbal and written information in detail about the setting, available treatment, assessment procedures, and study purposes. If they agree to participate, they will sign an informed consent form and then be screened for inclusion and exclusion criteria.

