### Sample size

Based on the power analysis (power=0.90), we estimated that the sample size of our study should be 212 participants (106 people per group) to detect differences between the two clinical groups. The power calculation was based on a moderate effect size (Cohen’ s d= 0.45) due to the naturalistic character of the study. A recent meta-analysis (58) established this value of Cohen’s d, calculating the effect size for borderline symptom trials as either 0.31 or 0.56, depending on the stand-alone or add-on design. Accessing these data, the authors decided to set the effect size as 0.45, which is a moderate value that is neither strict nor lenient. Before we reach the aforementioned sample size, we start processing our data within subjects, where a smaller sample size of 158 participants (79 per group) is needed to obtain a significant power of 0.80. The software used to calculate the power was R version 4.0.3.

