### Statistical analyses

#### Assessing the comparability of the two groups

Prior to the initiation of treatment, i.e., at baseline, the two groups will be compared for potential differences in all primary and secondary outcome variables: severity of BPD symptoms, self – harm and suicidality, severity of psychopathological symptoms, quality of life, quality and intensity of interpersonal relationships, functioning and disability. Due to being many outcome variables, MANOVA will be employed. Moreover, the two groups will be compared for potential differences in various socio-demographic variables as well as the presence of physical illness and details of the medication regime for BPD, by employing t-tests for independent samples. In line with this, socio-demographic and other variables that are significantly different between the two groups will be considered to be confounder variables and will be inserted as such in all ensuing analyses.

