#### Mediation analysis

Mediation analysis will occur through regression models, path analyses and the Sobel test. For each of the outcomes, three mediation analyses will be performed, with independent variable being the group assignment, In Model 1, the mediator will be reflective functioning, in Model 2, the defense style and in Model 3, the personality organization.

Mediation analysis will occur at T_2_, T_4_, T_6_, T_8_, T_10_ Moderation

In the multiple linear regression models described in the Evaluation of Effect, in the predictor variables, an interaction term between group assignment and age will be inserted as well.

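### Apart from the baseline outcome, covariates enter the effect models of this non-randomised comparison only if they differ significantly at baseline, so measured prognostic imbalances can go unadjusted

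*Protocol article*

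**What the plan says.** All references are to the protocol article.

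- **Design (text after Figure 1).** The baseline outcome is adjusted for unconditionally: "As the design does not include random allocation of participants in the two arms, baseline measurements of the outcome variables will be considered as confounders". A list follows: sex, family status, education, number of children, profession, living arrangement, physical illness, BPD medication and prior hospitalisation. For these the rule is "Those variables with a statistically significant difference between the two groups, will be considered confounder variables in the design".
- **Assessing the comparability of the two groups.** The significance rule is repeated. Socio-demographic variables, physical illness and medication details are to be compared "by employing t-tests for independent samples".
- **Evaluation of effect.** The regressions contain the baseline outcome, treatment duration, number of sessions and whichever covariates passed the screen.
- **Limitations and challenges.** Twice, the criterion is instead a substantial difference between groups, with no threshold.
- **Age.** The Aims section names it as a moderator and says that symptoms tend to decline with age. The moderation text says that "in the predictor variables, an interaction term between group assignment and age will be inserted as well". Limitations adds that an age effect, if confirmed, will be taken into account. Age is not on the Design list.
- **Early trauma.** The Assessments section says that the Early Trauma Inventory will be given at baseline. No analysis uses it.

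**The concern.** Whether a covariate confounds depends on its imbalance and on its relation to outcome. A p-value reflects the imbalance and the sample size, and nothing about outcome. A strong predictor with a moderate imbalance can therefore be left out while an irrelevant variable with a chance difference is kept. In a randomised trial this would mostly cost precision. Here, adjustment for measured covariates is the main protection of the primary comparison, and the rule decides it by a test with little power against moderate imbalances.

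Two further defects concern the same rule. The two criteria, significant and substantial, can select different covariates from the same data. And an independent-samples t-test has no meaning for a variable with several unordered categories, such as family status, profession or living arrangement; for binary sex the problem is smaller.

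**Working it through.** **Inputs from the article.** "Based on the power analysis (power=0.90), we estimated that the sample size of our study should be 212 participants (106 people per group"; "the authors decided to set the effect size as 0.45"; and for an earlier look, "where a smaller sample size of 158 participants (79 per group) is needed to obtain a significant power of 0.80". All tests are two-sided at 5%, which covers the baseline tests. The article gives no imbalance sizes or covariate–outcome associations; those below are assumptions.

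**1. The plan's own figures.** The two-sample t calculation at d = 0.45 gives 104.7, so 105 per group (210) for power 0.90, and 78.5, so 79 per group (158) for power 0.80. The stated 212 and 158 are consistent with this. Power at 106 per group is 0.906 (normal approximation).

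**2. How often the screen catches a true imbalance δ (in SD).** The standard error of the observed difference is √(2/106) = 0.137, so an observed difference must exceed 1.96 × 0.137 = 0.27 SD to be adjusted for. P(flag) ≈ Φ(δ/0.137 − 1.96), with a negligible second tail. The t-test version gives:

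| True imbalance | Flagged, 106 per group | Missed | Flagged, 79 per group |
|---|---|---|---|
| 0.20 SD | 31% | 69% | 24% |
| 0.25 SD | 44% | 56% | 35% |
| 0.30 SD | 58% | 42% | 47% |

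A binary covariate at 30% against 40% is flagged 33% of the time with 106 per group.

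**3. Bias left by the screen, with the baseline outcome carrying none of it.** Assume five independent confounders, each with δ = 0.20 SD in the same direction and r = 0.25 with outcome, and no true effect.

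- With no adjustment the bias is 5 × 0.20 × 0.25 = 0.25 SD.
- Under the screen, a covariate contributes only when its observed difference is below 0.269. With the upper limit at (0.269 − 0.20)/0.137 = 0.505 standard errors, the expected unadjusted difference per covariate is 0.20 × 0.693 − 0.137 × (0.351 − 0.001) = 0.090.
- The bias is 5 × 0.25 × 0.090 = 0.11 SD. Simulation (4,000 runs) gives 0.118 SD and a type I error of 12.6%. Adjusting for all five removes the bias and returns the type I error to about 5%.

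**4. The same, with the baseline outcome in the model, as the plan has it.** Assume that the confounders relate equally to baseline and follow-up, and let ρ be the residual correlation between the two. The confounders explain 5 × 0.25² = 0.3125 of the variance, leaving 0.6875. The share of their effect not carried by the baseline value lies between 0.6875(1 − ρ), when none of them is in the model, and (1 − ρ), when the others are. Multiplying by 0.113:

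| ρ | Bracket for the bias (SD) | Simulated bias (SD) | Simulated type I error |
|---|---|---|---|
| 0.3 | 0.05 to 0.08 | 0.06 | 7.4% |
| 0.5 | 0.04 to 0.06 | 0.04 | 6.2% |
| 0.7 | 0.02 to 0.03 | 0.03 | 6.7% |

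The Monte Carlo standard error of these type I errors is about √(0.07 × 0.93/4000) = 0.4 percentage points, so their order means little.

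**5. Against the planned effect.** 0.03/0.45 = 7%; 0.06/0.45 = 13%; 0.12/0.45 = 27%.

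These runs isolate the screen. They leave out treatment duration and number of sessions, which the plan also puts in every model.

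**The case against.** The plan is not unprotected. The baseline outcome is always in the model and removes part of any confounding by severity. Prior hospitalisation is a candidate, and the baseline Suicide and Self-Harm Inventory covers six months, with psychiatric admissions counted in the parasuicidal definition. Limitations concedes selection bias and unknown confounding, and says that consultation with a statistician and more robust methods are to follow. All this stands, and it reduces the size of the problem. It does not repair the rule, because the concession concerns unknown confounders and the screen discards known, measured ones.

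Several stronger readings are tempting, and the documents do not support them.

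- *A reader might take 0.12 SD and a 13% type I error as properties of this plan.* They arise only when the baseline outcome carries none of the association. Having all five imbalances point the same way is also an assumption.
- *A reader might infer that age is ignored, or that the group coefficient becomes the effect at age zero.* Age is in the models through the interaction, and the open reference to various socio-demographic variables could admit it to the screen. The age-zero reading needs an age main effect with uncentred age, and neither is stated. Such detail is commonly left to the full analysis plan.
- *A reader might infer that nothing guards against regression to the mean in self-harm and admissions.* The baseline measures just named give partial control.
- *A reader might infer that referral routes separate the arms.* The article does say "The two TAU centers receive referrals from the psychiatric emergency room, inpatient psychiatric unit, or other outpatient clinics of the two hospitals", but its next sentence adds private practitioners, who also refer to the intervention site. That site's public-sector sources may include emergency or inpatient services.

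**Conclusion.** The concern holds as a fault in a stated rule. It does not show that the estimate will be biased. The screen leaves a true imbalance of 0.20 to 0.30 SD unadjusted in 69% to 42% of trials with 106 per group; this follows from the article's sample size and significance level alone. The consequence for the treatment effect rests on assumptions. It is about 0.03 to 0.06 SD, with a type I error of about 6% to 7%, under five same-direction confounders that relate equally to baseline and follow-up. It reaches about 0.12 SD at most in that scenario if the baseline value carries none of the association. Fewer or weaker confounders, or imbalances that offset each other, would give less. The actual size and direction are unknown.

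The conflict between the two criteria and the t-tests on nominal variables need no assumption. Nor does the absence of age from the confounder list, or of any stated use for the trauma score. Because adjustment is the main defence of a non-randomised comparison, the rule should be changed before outcome data are analysed.

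**What to change.** - Delete the significance screen in Design, in Assessing the comparability of the two groups and in Evaluation of effect, and the substantial-difference wording in Limitations.
- In every effect model, whatever the p-values, adjust for one prespecified set chosen on subject-matter grounds from data already planned at baseline: baseline value of the outcome, age, sex, education, family or living status, profession, physical illness, BPD medication, prior hospitalisation and Early Trauma Inventory score. Keep or drop number of children, now on the list, on the same grounds.
- Describe baseline balance with standardised differences in place of t-tests, entering nominal variables by category.
- Fit the group-by-age term in a separate moderation model that includes an age main effect.
- Referral source may be added where it is recorded. It partly tracks arm, so it can correct only part of the selection.

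The cost is analysis wording and some degrees of freedom out of 212. The exact number depends on how many categories the nominal variables have, which the article does not give, but the loss of precision should be small. No new assessment is needed unless referral source has to be taken from the referral record.

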### Recruitment

Patients will be recruited from the participating centers. The STP-BPD at the Eginition Hospital receives referrals from public sector psychiatric health services and mental health private practitioners from Athens and the surrounding area. Occasionally, the program receives referrals from other regions of Greece, but for acceptance, a patient must maintain residency in Athens for a minimum of 2 years. The two TAU centers receive referrals from the psychiatric emergency room, inpatient psychiatric unit, or other outpatient clinics of the two hospitals (the Attikon General University Hospital and the Sismanogleion General Hospital, respectively). They also receive referrals from private mental health practitioners. The two TAU centers are located in different areas of Athens, TAU1 in the northern suburbs of Athens and TAU2 in the western suburbs of Athens, thus covering a population from a wide area of Athens and its surroundings with different socioeconomic characteristics. Patients who are already receiving BPD treatment at participating centers will not be included in the study.

All potential participants will be given verbal and written information in detail about the setting, available treatment, assessment procedures, and study purposes. If they agree to participate, they will sign an informed consent form and then be screened for inclusion and exclusion criteria.

### Participants

Patients are eligible if they (i) are between 18 and 55 years of age, (ii) have a primary diagnosis of BPD (diagnosed via the Structural Clinical Interview for the Diagnostic and Statistical Manual of Mental Disorders, 5^th^ version [DSM-5], Personality Disorders; [SCID-5-PD]) (57), and (iii) are willing to participate in the study.

The study will exclude patients with the following conditions (1): lifetime psychotic disorder (excluding a brief psychotic disorder as described in the DSM-5, BPD criterion 9 (1)); (2) bipolar disorder type I; (3) antisocial personality disorder; (4) severe substance dependence leading to severe cognitive limitations during therapy, requiring clinical detoxification; (5) an IQ below 80; (6) organic brain disease; and (7) poor Greek language skills. After referral, following the routine clinical practice of the participating centers, patients will initially be screened for inclusion and exclusion criteria by two experienced psychiatrists in one or two clinical interviews. The SCID-5-PD (57) will then be administered by well-trained, experienced psychologists in separate sessions (see **Table 1**).

**Table 1 T1:** Lists all the measures and their administration dates.

Measure	Screening	T0 (B*)	T1 (6m**)	T2 (1y***)	T3 (18 m)	T4 (2y)	T5 2y6m	T6 3y	T7 3y6m	T8 4y	T9 4y6m	T10 5y
Demographics	✔											
Clinical Interviews (for inclusion & exclusion criteria assessment)	✔											
SCID-5-PD	✔											
BPDsi-IV		✔	✔	✔	✔	✔	✔	✔	✔	✔	✔	✔
Suicide and Self-Harm Inventory		✔	✔	✔	✔	✔	✔	✔	✔	✔	✔	✔
BSI-53		✔	✔	✔	✔	✔						
WHOQOL- BREF		✔	✔	✔	✔	✔						
IIP-64		✔	✔	✔	✔	✔						
WSAS		✔	✔	✔	✔	✔						
WHODAS 2.0		✔	✔	✔	✔	✔						
EuroQol-5D-3L		✔	✔	✔	✔	✔						
Cost Interview		✔	✔	✔	✔	✔						
RFQ		✔		✔		✔						
DSQ-40		✔		✔		✔						
IPO-GR		✔		✔		✔						

*Baseline, **month, ***year

### Sample size

Based on the power analysis (power=0.90), we estimated that the sample size of our study should be 212 participants (106 people per group) to detect differences between the two clinical groups. The power calculation was based on a moderate effect size (Cohen’ s d= 0.45) due to the naturalistic character of the study. A recent meta-analysis (58) established this value of Cohen’s d, calculating the effect size for borderline symptom trials as either 0.31 or 0.56, depending on the stand-alone or add-on design. Accessing these data, the authors decided to set the effect size as 0.45, which is a moderate value that is neither strict nor lenient. Before we reach the aforementioned sample size, we start processing our data within subjects, where a smaller sample size of 158 participants (79 per group) is needed to obtain a significant power of 0.80. The software used to calculate the power was R version 4.0.3.

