**Method and design:**

A quasi-experimental clinical trial will be conducted. The study is designed to include 212 BPD patients who will be non-randomly assigned to specialized health care services and to two TAU centers. Patients will be recruited at each site following the routine clinical pathways of referral at each center. The primary outcome measures are BPD severity, suicide attempts and hospital admissions. The secondary outcome measures will include measures of general psychopathology, psychosocial functioning, quality of life and retention in treatment. In addition. An economic evaluation from a societal perspective will be conducted.

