### Primary outcome measures

The primary outcome measures include the severity of BPD and severe parasuicidal behavior. 331 The BPDSI (Borderline Personality Disorder Severity Index-Leibniz Institute for Psychology) (64) is a semi structured clinical interview measure that captures specific BPS symptoms over the past three months. It contains 70 items, which are similar to the DSM-IV criteria. It covers nine areas of symptoms: *(1) abandonment; (2) interpersonal relationships; (3) identity; (4) impulsivity; (5) parasuicidal behavior; (6) affective instability; (7) emptiness; (8) outbursts of anger; and (9) dissociation and paranoid thoughts* (64). For its reliability, the internal consistency is greater than alpha = .90 (total score) or between alpha = .49 and.89 (subscales) (65). It is a reliable and valid instrument that is suitable for use as an outcome measure (64, 66). In our sector’s validation procedure of the BPDsi (67, 68), the statistical analyses revealed a fairly valid and reliable tool (Cronbach’s α = .99). A cutoff score of 15 between patients and controls has been established; thus, a score below 15, which is rated two years after randomization or earlier and maintained until follow-up, is used as a criterion for recovery (64).

**Suicide and Self-Harm Inventory** (69): The purpose of the interview is to collect accurate data about attempted suicides and self-harm incidents over a six-month period without attempting to measure their severity. Bateman and Fonagy (70, 71) define parasuicidal behavior as including three types of behavior: *1) suicide attempts (which must be intentional, life-threatening, and require medical intervention); 2) life-threatening self-harm behaviors (which must be intentional, cause visible tissue damage, and require nursing or medical intervention); and 3) admissions to a psychiatric hospital*. The Greek version will be used here (72).

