#### Evaluation of effect

For evaluating the effect of the group assignment (intervention *vs* control) on the primary and secondary outcome variables, multiple linear regression models will be computed for each outcome variables. As predictors the following variables will be inserted: the baseline measurement of the outcome variable of interest, treatment duration, number of sessions attended and all variables that emerged as confounders at baseline (i.e. socio-demographic and other variables that were significantly different across groups).

This analysis will be replicated for all evaluation time points: T_1_ – T_4_. For time points T_6_-T_10_, it will occur only for the two primary outcome variables.

At the end of the study, a Repeated Measures ANOVA with the group assignment (IV) and the 11 time points of assessment (baseline, T_1_ – T_10_) will be performed for the two primary outcome variables.

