#### Dropout rates

Dropout rates will be compared at the end of the study with the non-parametric criterion Mann Whitney (IV: group assignment and DV: number of drop outs), as number of drop-outs is an ordinal variable.

The Statistical Package for the Social Sciences (SPSS) version 25 (95) will be used for the statistical analyses. All significance tests will be two-tailed, with a 5% significance level and 95% confidence interval.

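### The stated 90% power rests on a borderline-symptom effect size and supports only the BPD severity score; nothing in the protocol supports it for the event-based second primary outcome

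*Protocol article*

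**What the plan says.** The Sample size section states: "Based on the power analysis (power=0.90), we estimated that the sample size of our study should be 212 participants (106 people per group"). It justifies d = 0.45 from a meta-analysis "calculating the effect size for borderline symptom trials as either 0.31 or 0.56, depending on the stand-alone or add-on design", after which "the authors decided to set the effect size as 0.45". No other effect size appears. The Dropout rates section sets the error rate: "All significance tests will be two-tailed, with a 5% significance level and 95% confidence interval".

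There is more than one primary outcome. The abstract says: "The primary outcome measures are BPD severity, suicide attempts and hospital admissions". The Design section says: "Primary outcomes will be (i) the severity of BPD symptoms and (ii) the severity of self-harm and suicidality". Under Primary outcome measures, the Suicide and Self-Harm Inventory is said to "collect accurate data about attempted suicides and self-harm incidents over a six-month period", and the same sentence adds that severity is not measured. The parasuicidal behaviour defined there includes psychiatric admission. The second primary outcome is therefore made up of events in six-month windows.

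Under Evaluation of effect, each outcome is analysed by multiple linear regression with its baseline value as a predictor, and "This analysis will be replicated for all evaluation time points". At the end of the study, a repeated-measures ANOVA over 11 time points is planned for the two primary outcomes.

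**The concern.** A power figure belongs to an outcome, an effect and a test. Here a standardised mean difference for symptom scores is printed as the power of the study, while an event outcome of equal rank has no planning value at all. A difference of 0.45 standard deviations on a symptom scale says nothing about how far the rate of attempts, serious self-harm or admissions must fall.

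At stake is how the two-year results are read. Aims and hypotheses sets the primary aim over a two-year follow-up. For that period the event outcome gets four separate six-month tests, each using about a quarter of the follow-up events. If these are non-significant in a trial described as having 90% power, a reader may take them as evidence against an effect when the design could have missed a large one.

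**Working it through.** **1. The plan's own figure.** Inputs from the protocol: d = 0.45, two-sided 5%, power 0.90, 1:1 allocation.

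n per group = 2 × ((1.960 + 1.282)/0.45)² = 103.8, so 104. The exact t-test gives 105, and the protocol uses 106. Power at 106 per group is 0.903 (t-test). The 80% figure also reproduces: 79 per group gives 0.803. The arithmetic is sound for a continuous score.

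**2. Event outcome, one six-month window.** The documents give no event rates, so control risk p1 and risk ratio (RR) are assumptions. With n = 106 and p̄ = (p1 + p2)/2:

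Power = Φ{ [|p1 − p2| − 1.96·√(2p̄(1 − p̄)/n)] / √([p1(1 − p1) + p2(1 − p2)]/n) }

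Example, 20% against 10%: (0.100 − 1.96 × 0.0490)/0.0486 = 0.08, and Φ(0.08) = 0.53.

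The OR column converts the plan's own d: OR = exp(−0.45·π/√3) = 0.44. The last column solves the same formula for p2 at 90% power.

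| Control risk | RR 0.7 | RR 0.6 | RR 0.5 | OR 0.44 | Risk needed for 90% power |
|---|---|---|---|---|---|
| 10% | 12% | 19% | 28% | 32% | 0.3% |
| 20% | 21% | 35% | 53% | 54% | 5.3% |
| 30% | 32% | 53% | 75% | 68% | 12.0% |
| 40% | 45% | 71% | 89% | 78% | 19.8% |
| 50% | 60% | 85% | 97% | 82% | 28.5% |
| 60% | 75% | 94% | 99.5% | 84% | – |

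**3. Could d = 0.45 apply directly to event counts?** For over-dispersed counts with mean m and dispersion k, the variance is m + k·m². The standardised difference for a halved rate is 0.5m divided by the root of the average of the two variances.

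- m = 0.1, k = 3: 0.05/√((0.130 + 0.0575)/2) = 0.16.
- m = 0.5, k = 1: 0.25/√((0.750 + 0.3125)/2) = 0.34.
- m = 2, k = 1: 1/√((6 + 2)/2) = 0.50.

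So even a halving falls short of 0.45 when events are infrequent, and can exceed it when they are frequent.

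**4. Separate windows against pooling.** Simulated gamma-Poisson counts, assumed control mean 0.2 per six months, rate halved, 106 per group, no dropout. A t-test on counts stands in for the planned linear model. A t-test on the T0–T10 total stands in for the ANOVA group effect.

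| Scenario | One later window | 24-month total | Five-year group effect |
|---|---|---|---|
| Dispersion 1, effect from the start | 41% | 85% | 93% |
| Dispersion 3, effect from the start | 33% | 60% | 61% |
| Dispersion 1, no effect in first window | about 41% | about 56% | 84% |
| Dispersion 3, no effect in first window | 33% | about 35% | 50% |

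If only half the participants have complete data at five years (53 per group), the five-year figure falls from 93% to 65% in the first row. Simulated values vary by a point or two between runs.

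**The case against.** Four points can be made against this.

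- **The range depends on assumed rates.** This stands. A reader might infer that power for the event outcome is 20–75% in general. The documents do not support that: it fits control risks of 20–30% with risk ratios of 0.7 to 0.5. Nor do they show that events are uncommon. The outcome combines several behaviours, TAU referrals include the emergency room and inpatient unit, and the Limitations section describes severe BPD. A halving from 40–50% gives 89–97%.
- **A pooled analysis already exists.** This stands in part. A reader might infer that the events are never combined, but the planned ANOVA's group effect does combine them. In the simulation without dropout it does at least as well as a 24-month total. It comes only at five years, however, and loses much of its power if many participants are incomplete. It does not serve the two-year aim.
- **Pooling 24 months is not a free gain.** This stands. The first 6–8 months of STP-BPD are preparatory, with monthly sessions, and TAU is also monthly. If the groups differ little then, the first window dilutes the total, and at dispersion 3 the gain disappears.
- **The two-proportion test is not the planned test.** True: the plan names no any-event endpoint and uses baseline-adjusted linear regression, and adjustment could raise power. If d = 0.45 held for the counts, power would be about 90%. The protocol offers no basis for assuming so.

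**Conclusion.** The point holds in a limited form. The 0.90 is correctly computed and is supported for the BPD severity score. For the second primary outcome it has no support, because no event rate or effect size is stated. Its power in a single window could be far below 90% or above it: 12% to 97% across assumed control risks of 10–50% and risk ratios of 0.7 to 0.5. At the odds ratio equivalent to d = 0.45 it stays below 90% for every control risk tried from 10% to 60% (32–84%).

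A reader might go further and call the trial underpowered for suicidality. The documents do not establish that, since the answer turns on rates they do not give. What they do establish is that a study-wide figure is printed on evidence for one of the primary outcomes, and that no planned analysis of the event outcome pools its windows up to two years.

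**What to change.** 1. Keep 212. In Sample size, state that power 0.90 at d = 0.45 applies to the BPDSI score only. For the event outcome, print the detectable difference with 106 per group over a range of control rates, labelled as assumptions, in the manner of the last column of the first table.
2. In Evaluation of effect, add one pooled comparison of event counts over the 24 months from T0 to T4, with observed time as offset, as the main two-year analysis of the event outcome. Keep the per-window results as description and the five-year ANOVA as planned.

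This needs wording changes and one model on data already scheduled, with no extra participants or visits. The stated power for the second primary outcome becomes less favourable. The total does not show when an effect appears, though the per-window results still do. It is diluted if the preparatory phase brings little contrast, so its gain over one window may then be small or nil, and the text should say so.
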